### Data collection and follow-up

Two outcome assessors (primary investigator and one research assistant) perform all baseline and follow-up assessments. Before and during data collection outcome assessors train together the test procedures of objective outcomes to unify performance and interpretation. Also, thoroughly described test protocols for the objective outcome measurements are prepared.

*WOSI* Western Ontario Shoulder Instability Index; *EQ-5D-5 L* EuroQol 5 dimensions; *GPE* Global Perceived Effect

### Primary outcome measure

The primary outcome measure is change from baseline to 12 weeks in the total score of the patient-reported outcome measurement the WOSI. The WOSI covers 21 items, ranging from 0 to 2100 (0 = no trouble) [34] (Table 1). The WOSI has been translated and adapted for use in Denmark, according to international guidelines, before inclusion of patients [40]. The WOSI is a relevant outcome measure due to its capability of capturing changes in disease-specific aspects of QoL in shoulder instability (activity-related shoulder symptoms, such as the ‘feeling of slipping’ and ‘being unable to trust the shoulder’) [41, 42]. As such, the WOSI is generally recommended as a patient-reported outcome when evaluating treatment effects of shoulder instability [43].

### Key secondary outcomes

A number of secondary patient-reported outcome measures are obtained: the four individual domains of the WOSI covering: 10 items in ‘Physical symptoms’ (0–1000), 4 items in ‘Sport/recreation/work’ (0–400), ‘Lifestyle’ (0–400) and ‘Emotions’ (0–300), with the level of ‘no trouble’ equal to 0 accounting for all domains [34]. Also, fear of movement and reinjury is evaluated with the use of Tampa Scale of Kinesiophobia (TSK; 17–68, 68 = highest fear of movement and reinjury) [44, 45], in addition to pain intensity at rest, within the latest 24 h and 7 days, respectively, using a Numeric Pain Rating Scale (NPRS; 0–10 score, 10 = worst imaginable pain) [46], besides patient-rated important activity with the Pain Specific Function Scale (PSFS, 0–10 score, 10 = no problems in performing the activity) [47]. For cost-effective analysis the total score of the EQ-5D-5 L (−0.59 to 1 score, −0.59 = lowest health-related quality of life) is used, whereas QoL is measured with the EQ-5D Visual Analogue Scale (EQ-VAS; 0 to 100, 0 = lowest health-related quality of life) [48].

Secondary objective outcome measures obtained (Table 1) are the Constant-Murley Shoulder Score (CMS; 0–100 score, 100 = best possible shoulder function [49], as used for self-reported and objective shoulder function. For comparison to normative data, strength and range of motion measurements were also obtained for the noninjured shoulder according to the CMS protocol [49]. Additionally, participants are screened for generalised joint hypermobility (GJH) with the use of Beighton’s criteria tests and criteria (0–9 score, <4 = no GJH) [50]. Beighton’s criteria have shown to be reliable for measuring GJH [51]. Specific evaluation of anterior shoulder instability is performed by the clinical tests apprehension, relocation and surprise (positive? yes/no) [52–54]. Finally, proprioceptive shoulder function is tested with the upper extremity in an open kinetic chain. Briefly, the test is performed as follows: patients are blindfolded and asked to actively reproduce different shoulder angles within low ranges of shoulder flexion and abduction (low equal to 60° ± 10°) using a laser beam pointing at a target scale. This method has previously shown satisfactory reliability [55] (Table 1).

### Sample size and power considerations

This study was designed as an exploratory (superiority) trial with two groups (SINEX and standard care) using the WOSI questionnaire, as recommended in clinical trials of shoulder instability patients [19, 43, 56]. The power and sample size calculation is based on the differences in the WOSI change score between the two groups from baseline to the 12-week follow-up.

It is expected that the group allocated to SINEX will improve 250 points more than the group allocated to standard care based on the primary outcome the WOSI at endpoint after 12 weeks. With a mean baseline WOSI score expected to be 1100 points (range 0–2100, with 2100 as worst possible score) and a common standard deviation assumed to be 320 [57], a sample size of 36 participants per group is required to detect a statistical difference (significance level of 0.05, two-sided, with 90% power). To account for possible barriers, noncompliant patients and participants lost-to-follow-up, it was decided to enrol a total sample size of 80 participants (40:40). For practical logistical reasons, new patients will no longer be included in the study after March 2017.

### Statistical evaluation

Primary analysis will be performed at the primary endpoint (12-week intervention period).

All descriptive statistics and tests will be reported in accordance with the recommendations of the ‘Enhancing the QUAlity and Transparency Of health Research’ (EQUATOR) network [35]; i.e. various forms of the CONSORT guidelines [58].

All primary analyses will follow the intention-to-treat principle; i.e. all participants in the trial will be included in the analysis according to the group to which they are randomised, regardless of dropout/any departures from allocated treatment. Missing data will be replaced using a nonresponder imputation, in which the baseline value is carried forward [59]. The rationale behind this type of analysis builds on the assumption that those who dropped out returned to their baseline WOSI score [60]. For sensitivity and exploratory purposes also a per-protocol analysis, including those with good compliance (as previously described) with the protocol (including outcome assessments available after 12 weeks) will be performed.

An analysis of covariance (ANCOVA) model will be used to analyse mean changes in continuous endpoints. The model will include treatment, study centre, and status with respect to type of dislocation as fixed effects, with the baseline value of the relevant variable as a covariate. Categorical outcomes for dichotomous endpoints will be analysed with the use of logistic regression with the same fixed effects and covariates as the respective ANCOVA.

For the longitudinal part of the trial a linear mixed ANCOVA model with repeated measures of the WOSI (4, 8 and 12 weeks) will be performed to test the difference over time between the intervention and the control group; interaction: Group × Time, with the same fixed effects and covariates as the respective ANCOVA. For these analyses the ‘data as observed’ will be applied (i.e. no imputation for missing data needed). An alpha level of 0.05 will be considered as being statistically significant (*p* < 0.05, two-sided). The data analysts will be blinded to the allocated interventions for primary analyses. In general, results will be expressed as the difference between group means with 95% confidence intervals and the associated *p* values.

Data analyses will be carried out according to a pre-established analysis plan, publicly available before the final patient is included, and analysed with the use of SAS software (SAS Institute Inc., Cary, NC, USA).

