### Study objectives

The aim of this randomised controlled clinical trial is to evaluate the efficacy and safety of a 12-week, structured ‘Shoulder Instability Neuromuscular Exercise’ (SINEX) programme versus 12 weeks of a self-managed, training-based, shoulder exercise programme (‘standard care’), measured on the Western Ontario Shoulder Instability Index (WOSI) questionnaire [34] in patients with TASD (primary and recurrent). It is hypothesised that patients receiving 12 weeks of SINEX training will show superior improvement in short- and long-term shoulder-related QoL and function.

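### The longitudinal WOSI model names only a Group × Time test over weeks 4, 8 and 12, which asks whether the group difference changes after week 4, not whether the groups differ

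*Protocol article*

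**What the plan says.** All of this stands in the Protocol article, Statistical evaluation.

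- **Primary analysis.** An ANCOVA of change at 12 weeks, by intention to treat, with missing values replaced by the baseline value. Its fixed effects are treatment, centre and primary or recurrent injury, and the model is adjusted "with the baseline value of the relevant variable as a covariate".
- **Longitudinal analysis.** "a linear mixed ANCOVA model with repeated measures of the WOSI (4, 8 and 12 weeks) will be performed", its purpose being "to test the difference over time between the intervention and the control group; interaction: Group × Time". It is fitted "with the same fixed effects and covariates as the respective ANCOVA. For these analyses", so baseline WOSI enters as a covariate. Week 0 is collected (Table 1) but is not listed among the repeated outcomes.
- **Missing data in this model.** "For these analyses the ‘data as observed’ will be applied", without imputation.
- **Reporting.** A general sentence says that results will be shown as differences between group means with 95% confidence intervals and p values. It names no visit, and no average over visits, for the longitudinal model.

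Study objectives states the hypothesis that SINEX patients "will show superior improvement in short- and long-term shoulder-related QoL and function".

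**The concern.** A Group × Time interaction carries the treatment effect when baseline is one of the repeated outcomes: the groups start level, so any later separation is an interaction. Here baseline is on the right-hand side and only post-baseline visits are outcomes. In that model the interaction concerns only the shape of the group difference between weeks 4 and 12. Its level, which is what a group comparison needs, sits in the treatment term and the visit-specific contrasts, and the text singles out neither.

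The primary analysis carries baseline forward, and the per-protocol analysis keeps compliant patients with a week-12 assessment. The mixed model is therefore the only described WOSI analysis that is neither imputed nor restricted to compliers, and so the natural check on the primary result. With the interaction as its only named test, it does not provide that check. A non-significant interaction beside a significant ANCOVA could be read as a contradiction when it is none. Under Blinding, results are to be interpreted before allocation is revealed, so the inference should be settled beforehand.

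**Working it through.** **Inputs from Sample size and power considerations:** difference 250 points at week 12; common SD 320; two-sided alpha 0.05; 90% power; 36 per group required; 40 per group enrolled.

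**Assumptions, not in the document:** SD 320 at each visit after adjustment; equal correlation ρ between visits; no missing visits; the time profiles of the group difference.

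**1. The plan's own figure.** For a two-sample t test the noncentrality is 250 / (320 × √(2/n)).
- n = 35: 3.27, power 89.6%.
- n = 36: 250/75.42 = 3.31, power 90.5%. The stated 36 per group reproduces.
- n = 40: 250/71.55 = 3.49, power 93.2%.

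The last two are also the power of a week-12 contrast from the longitudinal model under these assumptions.

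**2. What the interaction tests.** Let δ4, δ8 and δ12 be the adjusted group differences. The Group × Time null is δ4 = δ8 = δ12. With equal correlation, the 2-df F test has noncentrality

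λ = n / (2 × SD² × (1 − ρ)) × Σ(δj − mean δ)².

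If the three differences are equal, the sum is zero, λ = 0 and the rejection rate is alpha, whatever n, SD or ρ.

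**3. Numbers in.** With n = 40, SD = 320, ρ = 0.6, the multiplier is 40 / (2 × 102,400 × 0.4) = 0.000488; denominator df 2 × 78 = 156.

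| Difference at weeks 4/8/12 | Σ(δj − mean δ)² | λ | Group × Time rejects | Week-12 contrast rejects |
|---|---|---|---|---|
| 250/250/250 | 0 | 0 | 5% | 93% |
| 150/200/250 | 2 × 50² = 5,000 | 2.44 | 26% | 93% |
| 83/167/250 | 2 × 83.3² = 13,889 | 6.78 | 63% | 93% |
| 0/125/250 | 2 × 125² = 31,250 | 15.26 | 94% | 93% |
| 250/125/0 | 31,250 | 15.26 | 94% | 5% (no difference to find) |

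The last two rows have the same λ. The test cannot tell a benefit that builds to 250 points from one that has vanished by the primary endpoint.

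**4. Sensitivity to ρ.** Over ρ = 0.5 to 0.8 at 40 per arm, 150/200/250 gives about 22% to 49% and 83/167/250 about 53% to 92%. The constant profile stays at 5%.

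**5. Simulation check** (20,000 runs, 36 per arm, ρ = 0.5). Constant 250: interaction 5.0%, week-12 contrast 90.3%. Linear build-up 83/167/250: interaction 47.0%, against 48.5% by formula.

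**6. Source of the problem.** If week 0 is made an outcome with zero difference, the profile is 0/250/250/250, with sum of squares 187.5² + 3 × 62.5² = 46,875. At 36 per arm and ρ = 0.5, λ = 36/(2 × 102,400 × 0.5) × 46,875 = 16.5 on 3 df, and power is 94% (82% to 99.6% for ρ 0.3 to 0.7). The loss comes from pairing baseline as a covariate with a Group × Time test on post-baseline visits only.

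**The case against.** The superiority hypothesis is tested by the primary week-12 ANCOVA, on which the sample size rests, and nothing in the article makes the longitudinal model primary or confirmatory. A reader might infer that the trial's test of efficacy is invalid. The documents do not support that: the primary estimate, its power and its type I error are untouched. This stands, and it sets the severity.

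Read literally, a difference over time is what an interaction tests, and the text never says that this p value decides whether SINEX works. That is fair. The wording is open to both readings, but on either one the model has no named group comparison.

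The treatment term is in the model, and the general reporting sentence points towards mean differences, so visit-specific contrasts could be estimated. An analysis plan not shown may list them. This also stands in part. The complaint is confined to a stated choice: the interaction is the one test the article fixes.

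A reader might also infer that any sustained benefit would be missed. That goes too far. SINEX progresses through levels of difficulty over the 12 weeks, so a gradual build-up is plausible, and the table shows high power for a late one. Low power needs an effect largely present by week 4.

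Finally, the hypothesis mentions long-term benefit, from which one might infer that weeks 52 and 104 belong in this model. That is a separate design choice, since patients may seek other treatment after the intervention period, and it forms no part of this point.

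**Conclusion.** The point holds for the supportive longitudinal analysis and should be fixed. That a benefit held constant from week 4 is rejected at the alpha rate follows from the model as written and needs no assumption about correlation, SD or sample size. The intermediate figures (26% and 63% against 93%, or 90.5% for the week-12 contrast at 36 per arm) depend on the assumed correlation of 0.6, equal correlation between visits, SD 320 as the adjusted visit SD, complete data and the chosen profiles. A significant interaction does not show benefit at week 12, and a non-significant one is not evidence against SINEX.

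**What to change.** Keep the model and its terms. In Statistical evaluation and the analysis plan:

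1. State that inference from the mixed model is the adjusted group difference at week 12 with its 95% CI, with the differences at weeks 4 and 8 alongside.
2. Label this estimate as supportive of the primary ANCOVA, obtained from observed data and not with baseline carried forward.
3. State that Group × Time describes the time course and is not evidence for or against efficacy.

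The cost is two or three sentences and one contrast statement in the program. The small downside is a second week-12 estimate that may differ from the primary one, which is why its supportive role must be written down. The article reports that recruitment was still open when it was submitted and promises a public analysis plan before the last patient is included, so on that timetable the change can be made in advance.

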### Ethical considerations

Patients are informed about the randomised design with allocation to either of the two treatment arms and also about the content of the two treatment arms. Patients are kept blinded for any of the study hypotheses, which can be justified since patients are treated with either an anticipated equivalent, or superior, treatment to what they would have received if they did not participate in the study. Furthermore, both patient groups are expected to benefit from participation in the study through their respective interventions. The risk of sustaining another shoulder dislocation from participating in this study is not expected to be any higher than from regular daily activities. Furthermore, it is not anticipated that participation will cause any serious adverse events or harms. The trial will meet the criteria and principles of the Declaration of Helsinki (80) and has been approved by the local Ethics Committee for the Region of Southern Denmark (project ID: S-20140093). The trial is registered at ClinicalTrials.gov (ID; NCT02371928). Approval from The Danish Data Protection Agency is given (Journal number: 2015-57-0008)

## Discussion

Traumatic anterior shoulder dislocation is common and may decrease shoulder-related QoL. The aim of this randomised controlled clinical trial is to evaluate the efficacy and safety of a 12-week, structured, neuromuscular shoulder exercise programme versus 12 weeks of self-managed shoulder rehabilitation in patients with TASDs measured on the WOSI questionnaire.

The current study will shed light on the effect of nonoperative treatment for patients with primary and recurrent anterior shoulder dislocations and provide foundation for nonoperative treatment guidelines. Additionally, this trial will support evidence-based shared decision-making processes (between physicians and patients) in clinical practice, when patients seek orthopaedic and/or physiotherapy treatment for a primary or recurrent anteriorly dislocated shoulder.

Previously, only one level-II study has succeeded in managing TASD patients (average age 19 years) nonoperatively by including 12 weeks of specific shoulder rehabilitation exercise. At an average time to follow-up of 3 years 15 out of 20 patients (75%) had not redislocated their shoulder and had returned to sport within an average time of 3 months [61]. Thus, supervised and adequate progressive shoulder rehabilitation, therefore, seems evident following a TASD, but has not yet been documented in a high-level study such as in the current trial. Finally, no matter the treatment (operative as well as nonoperative), fear of movement and reinjury, mood, social support and self-motivation has shown to greatly influence the decision on return to sport [14]. Aspects like these are only covered by patient-reported outcomes, supporting the use of a patient-reported outcome as primary treatment effect measure in the current trial.

One limitation of the present trial may be that since little is known about the nonoperative treatment potential for patients with recurrent shoulder dislocation, the pragmatic choice of including patients with up to a maximum number of five dislocations may be too broad; although, orthopaedic surgeons will screen each patient before enrolment to make sure that no patients with injuries warranted for shoulder surgery are included. Furthermore, to secure an even distribution of primary and recurrent dislocation patients in each treatment group stratification techniques are used. Finally, as in similar exercise trials, it is not possible to blind either patients or physiotherapists to the treatment allocation. Thus, only the testers can be blinded.

The study strengths are the rigorous inclusion criteria compared with previous trials of TASDs, aiming at a homogenous patient group with self-reported shoulder trouble. Due to the fact that not all patients experience post-traumatic shoulder trouble nor recurrent shoulder instability, unnecessary invasive procedures will not initially take place in the current study, as compared to previous RCTs performing immediate stabilising surgery [20–22]. Finally, the use of a standardised, individualised and physiotherapist-supervised neuromuscular shoulder exercise programme developed for accommodating all types of TASD patients (e.g. those with severe instability and pain and those in need of more sports-specific exercises), is an additional strength.

### Timeline, trial status and publication plan

Recruitment of patients began March 2015 and is expected to run consecutively until March 2017. At the time of submission of this study protocol (October 2016), the trial is ongoing and still recruiting patients. For the time being, 50 patients have been included in the project. Data will be analysed, interpreted and published regardless of whether results are positive, negative or inconclusive.

## Abbreviations

ANCOVA: Analysis of covariance
QoL: Quality of life
RCT: Randomised controlled trial
SINEX: Shoulder Instability Neuromuscular Exercise
TASD: Traumatic anterior shoulder dislocation
WOSI: Western Ontario Shoulder Instability Index
